## Abstract

**Background:**

In the UK and beyond, public funding is used to commission interventions delivered in public health early years settings aimed at improving health and well-being and reducing inequalities in order to promote school readiness. This is a key setting for obesity prevention programmes, which are often commissioned despite the limited evidence base. The HENRY (Health, Exercise, Nutrition for the Really Young) programme is an 8-week programme delivered to parents of preschool children, designed to support families to optimise healthy weight behaviours. Early evidence suggests that it may be effective, but a robust evaluation using a randomised controlled design has not been conducted. This study begins this process by evaluating the feasibility of conducting a multi-centre definitive trial to evaluate the effectiveness and cost-effectiveness of HENRY to prevent obesity in the early years.

**Methods:**

This is a multi-centre, open labelled, two group, prospective, cluster randomised, controlled, feasibility study aiming to recruit 120 parents from 12 children’s centres, based in two local authority areas. Within each of the two local authorities, three centres will be randomised to HENRY and three will be randomised to a control arm of standard care (usual provision of services within children’s centres). We will explore HENRY commissioning, provision and delivery and assess the feasibility of local authority, centre and parent recruitment, the processes and time required to train and certify staff to deliver the intervention, the potential sources (and associated risk) of contamination and the feasibility of the trial procedures. Research includes a process evaluation, feasibility of cost-effectiveness evaluation, with progression to the definitive trial judged against pre-defined criteria.

**Discussion:**

This feasibility study will support the decision to proceed to, and the design of, a future definitive trial, providing an evidence base of an approach to prevent childhood obesity, which has been deemed attractive to all stakeholders, including parents. Given the widespread adoption of the intervention, this has the potential to impact on public health in the UK and beyond.

**Trial registration:**

ClinicalTrials.gov Identifier NCT03333733 registered 6th November 2017

Protocol date: 25th October 2017

Protocol version: 4.0

## Background

Tackling obesity is a key global public health priority, with international, national and local strategies aimed at reversing the trend of rising rates of childhood obesity [1–3]. While treating obesity remains a priority, there are persuasive arguments for prevention during childhood. Establishing healthy behaviours in early childhood is essential to ensure optimal growth and development [4], and negative lifestyle behaviours that are developed early can persevere and are associated with chronic diseases in adulthood such as cardiovascular disease and type 2 diabetes [5]. Furthermore, once established, obesity is difficult to reverse [6], strengthening the case for prevention [7]. Interventions delivered in the first few years of life are therefore essential to impact the health of our children now and in the future [8].

Interventions aimed at preventing or treating obesity report inconsistent results [6, 9–13], though there is agreement that multi-component interventions especially those engaging parents have the greatest impact [6, 14]. Systematic review evidence has found that some efforts to prevent obesity have had disappointing results due in part, to inclusion of interventions which are not underpinned by a robust evidence-based and/or not rooted in behaviour change theory [6, 11–13, 15–17]. Intervention strategies are not always tailored to the most important and modifiable behaviours, and often, they are inadequate to change family, environmental and extrinsic factors in combination with health education strategies aimed at personal behaviours. Further, reviews indicate that there is a lack of careful pre-testing and formative evaluation procedures before larger-scale implementation and lack of involvement of stakeholders in the development. Interventions with greater involvement by parents/carers appear to offer the most promise in preschool children. The proposed feasibility study involves an independent evaluation of an existing preschool obesity prevention intervention, ‘HENRY’ (Health, Exercise, Nutrition for the Really Young). The HENRY organisation developed the HENRY programme in 2007 with the Department of Health and Department for Education support in the UK. It is an 8-week group-delivered programme provided to parents of preschool children and is currently commissioned and delivered across the UK by ~ 35 local authorities (approximately 10% of authorities) providing more than 190 programmes each year. Over 10,000 families have already participated. It is delivered in the community, predominantly by children’s centre staff [18]. HENRY uses a responsive approach to improve children’s centres environments and promote parenting skills aimed at enhancing family lifestyles. These intervention targets are consistent with literature in childhood obesity [7, 12, 13]. Preliminary data indicates that HENRY may be effective at reducing childhood obesity and improving family health [18], and research is underway evaluating engagement strategies with families [19]. However, research to date has not compared outcomes with those parents who have not attended HENRY; thus, further robust evaluation of effectiveness and cost-effectiveness using a RCT design is needed to establish its effectiveness.

Given the uncertainties associated with recruiting local authorities, service providers and children’s centres to a trial, it is necessary to conduct research in advance of a definitive multi-centre trial. The process of recruiting parents and conducting research in this setting also requires consideration, as models of commissioning and delivering HENRY are complex and vary by location. In some instances, HENRY is commissioned by local authorities and delivered by existing centre staff. In others, third sector or health providers may commission HENRY directly or locally employed HENRY staff may deliver programmes. This study will assess the feasibility of the planned recruitment rate at the local authority, children’s centre and parent level and ensure competence of programme delivery, in addition to providing vital information for calculation of the sample size for the future trial. There will also be a focus on identifying potential sources and risks of contamination and assessing the level of risk associated with each contamination source. A future trial will be used to offer commissioners an evidence-based intervention including a cost-effectiveness analysis, tested in children’s centres in the UK, and to provide much needed evidence on the effectiveness of early obesity prevention in public health settings.

## Methods/design

### Aim

This feasibility study aims to determine the feasibility of undertaking a definitive trial to evaluate the clinical and cost-effectiveness of the HENRY programme in preventing childhood obesity.

### Objectives

Primary objectives are the following:To determine whether it is feasible to recruit local authorities/service providers that are willing to nominate children’s centres to be involved in the research (allowing randomisation in place of the usual selection of centres in most need).To assess the time required to train and certify staff to competently deliver HENRY programmes, in order to propose a clear process and timeline for a definitive trial.To determine whether it is possible to recruit parents to the study, who are enrolled to attend a HENRY programme, and the practicality of recruiting parents to the study from control centres, where the pathway to recruitment is less defined compared to the HENRY centres.To explore HENRY commissioning, provision and delivery via postal screening questionnaires and qualitative data collection in areas currently delivering HENRY.To explore potential sources and risks of contamination, including the degree to which parents use multiple centres, the level of contamination resulting from social networks (control and HENRY parents sharing knowledge) and the possibility of HENRY-trained facilitators sharing knowledge with control centres.

Secondary objectives are the following:To examine the acceptability and completeness of the proposed methods of data collection to ensure they are feasible for a definitive trial.To gather data to allow estimation of the sample size requirements for the definitive trial.To assess the acceptability of the design for parents, commissioners and centre staff, particularly related to withholding HENRY training in control centres until the end of the study.To determine the practicalities of delivering the required number of HENRY programmes within the trial period in regard to programme implementation.

### Progression rules for definitive trial

Progression will be judged via a traffic light system whereby ‘Green’ indicates it is feasible to proceed to a definitive trial with the current trial design and procedures, ‘Amber’ indicates modifications are required to the trial design and/or procedures before proceeding to a definitive trial, and ‘Red’ indicates it is not feasible to proceed to a definitive trial.Recruitment of local authorities (and their service providers (if applicable)): Green = two local authorities within 12 months (beginning from receipt of ethical approval); Red = less than two local authorities within 12 months.Randomisation of children’s centres: Green = at least 12 centres randomised within 12 months (beginning from receipt of ethical approval); Amber= 8–12 centres randomised within 12 months; Red = less than 8 randomised within 12 months.Recruitment of parents: Green = an average of at least 4 parents registered per programme (or control group equivalent); Amber = 3 parents registered per programme; Red = less than 3 parents registered per programme.

Progression criteria have been approved by the steering committee. If any of the criteria are not met, future assessment of the effectiveness of the HENRY programme will be negotiated to decide if a definitive trial is feasible. If a definitive trial is supported, further feasibility testing may be needed prior to the conduct of a definitive trial should negotiations result in changes to the design based on failure to meet progression criteria. Our method for determining progression criteria are based on recommendations proposed by Avery et al. [20] in which these pre-specified criteria have been agreed with funders to determine progression to the definitive trial. Objectives related to staff training, collection of data and estimating sample size are included to support the design of a definitive trial, but do not have assigned progression criteria cutoffs. While important, they do not provide an indication of whether or not a future trial should proceed.

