### Design

This is a multi-centre, open labelled, two group, prospective, cluster randomised, controlled, feasibility study aiming to recruit 120 parents from 12 children’s centres (Fig. 1).

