**Fig. 1 Fig1:**
[figure not shown]
Flow chart of a cluster randomised controlled feasibility study evaluating feasibility/acceptability of a definitive trial to test effectiveness of HENRY (local authorities will be ask to nominate four or six centres, depending on availability of eligible centres)

As the progression criteria indicates, the feasibility study will monitor our ability to recruit centres and will therefore allow a local authority to allocate four rather than six centres in order to answer all objectives of the study. In this situation, trial progression criteria will be highlighted as ‘Amber’. Cluster randomisation has been chosen to reduce contamination as HENRY is a group-based intervention which aims to provide practical guidance and improve parenting skills, intended at enhancing family homes *and* children’s centre environments. In centres allocated to receive HENRY, parent recruitment and registration will be restricted to only those enrolled on a HENRY programme. Centre staff and participants will, of necessity, be aware of treatment allocation, but collection of outcomes will be performed by interviewers from the National Centre for Social Research (NatCen; a social research unit geographically located across the UK) who will be blinded to treatment allocation.

Within each of the two local authorities nominating six centres, three centres will be randomised to HENRY and three will be randomised to the control arm (training to deliver the HENRY programme in these centres will be made available (though not compulsory) at the end of the study). Historically, when HENRY is commissioned within an area, the local authority determines which centres will receive the intervention. In areas where HENRY is provided by external partners (e.g. charities such as Banardos), this is determined by the service provider. To maintain some autonomy for the commissioners, local authorities/service providers will be asked to allow randomisation of half of the centres they propose to the intervention and half to the control arm.

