#### Children’s centres

The inclusion criteria for children’s centres are as follows:Any type of children’s centre or other early years setting such as a nursery or community venue.Children’s centres must aim to run HENRY programmes starting within 4 weeks of training completion and aim to run three courses during the study.Children’s centre managers must agree to support participant recruitment within their centres. This will be evidenced by agreements signed by children’s centre managers

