#### Parents

Parents attending participating children’s centres will be approached by children’s centre staff, who will introduce the study.

In centres randomised to HENRY, parents will be recruited when they enrol to attend the HENRY programme. This procedure has been used successfully in the past and indicates that at least four parents within each programme will be eligible and will agree to take part in the study [18]. In centres that have been randomised to the control arm, parents will be recruited from other programmes that are running within the Centres such as ‘Stay and Play’. In both HENRY and control centres, staff will introduce the trial to parents and request that all parents approached complete a parent screening form collecting anonymised data on age range, ethnicity and basic eligibility criteria. Parents will indicate on the screening forms if they are interested in taking part in the study and, if interested, asked to provide consent to give their contact details to a NatCen interviewer for confirmation of eligibility. Parents will be informed that providing data collected for screening is not compulsory and that all data provided will remain anonymous.

Upon receipt of the parent screening forms (including their consent to be contacted), a local NatCen interviewer will call parents to provide further details of the study and confirm eligibility. NatCen are an independent social research agency (http://natcen.ac.uk) that has no role in delivery of the intervention. Informed written consent and recruitment will occur in parent’s homes and will be undertaken by interviewers from NatCen. Parents will be provided participant information sheets disclosing the full details of the study and their requirements including the feasibility nature of the study and its impact on future research. Prior to providing consent, they will be given time to discuss the study and ask any questions. All parents will have the right to refuse consent without giving reasons and will remain free to withdraw from the study at any time without giving reasons.

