### Statistical analysis

Recommendations for feasibility studies suggest that at least 30 participants per group will allow sufficient precision when estimating study summary measures [34]. We plan to recruit two local authorities and 120 parents to give confidence that a phase III multi-centre trial can be successfully conducted [34, 35].

As this is a feasibility study, the analysis will focus on descriptive statistics and confidence interval (CI) estimation rather than formal hypothesis testing (i.e. no formal evaluation of the study interventions will be conducted as part of this feasibility study). The trial is not powered to provide a precise estimate of the level of clustering relating to group effects, but it will allow an investigation of this effect, which will inform the sample size estimation for the definitive trial. No formal analyses are planned until after the trial is closed to recruitment and follow-up and the required number of local authorities/centres have been randomised and the required number of parents have been registered. Final analysis will be carried out when all available outcome data has been collected.

The feasibility and success of the recruitment strategy will be evaluated by summarising the screening, eligibility, consent and randomisation/registration processes, including the numbers of local authorities/centres/parents involved during each stage. Reasons for non-participation in the study will be summarised. The total number of parents registered will be summarised, overall, by month/programme (as appropriate) by centre and local authority. The length of time taken to train and certify staff to deliver the HENRY programme will be detailed by HENRY staff. The number of staff attending training/certified will be summarised overall and by centre. Facilitator response to training will be captured as part of the process evaluation.

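### At full planned delivery the 120-parent target works out at 3.33 parents per programme, which misses the Green cut-off of 4 and falls in no stated band

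*Protocol article*

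**What the plan says.** All references are to the protocol article.

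- **Target (Design):** a "feasibility study aiming to recruit 120 parents from 12 children’s centres". The text following Fig. 1 says that in each of the two local authorities nominating six centres "three centres will be randomised to HENRY and three will be randomised to the control arm", so six centres per arm.
- **Courses (Inclusion criteria, Children's centres):** centres must "aim to run three courses during the study".
- **Cut-offs (Progression rules for definitive trial):** "Green = an average of at least 4 parents registered per programme (or control group equivalent"; then "Amber = 3 parents registered per programme; Red = less than 3 parents registered per programme". No total number of parents and no number of programmes appears in any of the three progression criteria. The other two count local authorities and centres.
- **Expected yield (Recruitment and consent, Parents):** past use of the procedure "indicates that at least four parents within each programme will be eligible and will agree to take part in the study".
- **Basis for numbers (Statistical analysis):** a cited recommendation that "at least 30 participants per group will allow sufficient precision when estimating study summary measures", followed by the plan for 120 parents.
- **Fewer centres (Eligibility criteria):** four centres per local authority are acceptable, with the centre criterion then labelled Amber.

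**The concern.** The recruitment target and the Green cut-off are both fixed in the same document, and a reader would expect a study that delivers its plan and reaches its target to be Green. On the stated figures it is not. The result also has no colour at all, because averages above 3 and below 4 are assigned to no band.

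A second weakness is that the criterion is purely a ratio. Depending on what is counted in the denominator, running fewer courses could raise the score while the number of parents falls, and neither of the other two criteria looks at parents or courses.

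At stake is one of only three criteria that decide whether a definitive trial goes ahead with the current design. If the target is met and the committee has to argue afterwards over whether 3.33 is Amber or near enough to Green, the criterion has lost the benefit of being set in advance.

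**Working it through.** **Inputs:** 120 parents and 12 centres (Design); three courses per centre as an aim (Inclusion criteria, Children's centres); Green at 4 or more, Amber 3, Red below 3 (Progression rules); minimum of eight centres in total (Eligibility criteria, 2 x 4).

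**Assumption:** each control centre contributes as many control equivalents as a HENRY centre runs courses. The article does not state this.

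**Step 1. Can the target be reproduced from the plan's own yield?** Parents = centres x courses x parents per programme = 12 x 3 x 4 = 144, not 120. Solving for courses, 120 / (12 x 4) = 2.5 per centre, a figure the document does not give. The cited 30 per group gives 60 over two arms and does not produce 120 either.

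**Step 2. Where does the target fall?** 12 x 3 = 36 programmes or equivalents, and 120/36 = 3.33. Green needs 36 x 4 = 144, so the target is 120/144 = 83% of what Green requires. The literal Amber value of 3 corresponds to 36 x 3 = 108 parents. The target lies between 108 and 144, where no band is written.

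**Step 3. Does this depend on the control assumption?** In the HENRY arm alone there are 6 x 3 = 18 programmes. With an even split of parents (an assumption), 60/18 = 3.33, the same figure. For the HENRY arm alone to reach 4 it would need 18 x 4 = 72 of the 120.

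**Step 4. How does the result change with delivery?**

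| Centres | Courses per centre | Programmes | 120 parents gives | Parents needed for Green |
|---|---|---|---|---|
| 12 | 3 | 36 | 3.33 | 144 |
| 12 | 2 | 24 | 5.0 | 96 |
| 12 | 1 | 12 | 10.0 | 48 |
| 8 | 3 | 24 | 5.0 | 96 |

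**Step 5. What does the denominator do?** Take 48 parents from one course in each of 12 centres. Counting programmes delivered, 48/12 = 4.0, which is Green on this criterion with 48/120 = 40% of the target. Counting programmes planned, 48/36 = 1.33, which is Red. The rule does not say which count applies.

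**The case against.** The strongest reply is that the rule measures yield per programme while 120 is a total, and the two need not coincide. Three courses is an aim and not a fixed number. With an expected yield of at least four, 144 can be read as full capacity and 120 as a total that tolerates some undelivered courses. This stands in part: the table shows that 120 parents is Green at two courses per centre or with eight centres. It would therefore be wrong to infer that target and cut-off conflict at every level of delivery. But the document nowhere explains 120 in this way, and at the delivery it asks for, reaching the target still misses Green.

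Three other inferences are tempting and go further than the text allows.

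- **That a 48-parent study would pass.** This holds only if the denominator is programmes delivered, which is not stated, and it concerns one criterion of three. Delivery is a secondary objective in its own right, and the number of courses per centre is reported descriptively.
- **That 48 parents would breach a minimum of 30 per group set by the plan.** The figure of 30 is a cited recommendation about the precision of summary measures, not a progression threshold.
- **That strong HENRY recruitment could hide a failing control arm**, for example 6 per programme against 2, averaging 4. This assumes the arms are pooled over equal numbers of slots, which the rule does not say. The definition of the control equivalent may also be left to the full protocol, so its absence from an article is no finding.

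Finally, unmet criteria lead to negotiation and perhaps further feasibility testing. That limits the harm.

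**Conclusion.** The point holds in a bounded form. At 12 centres and three courses each, the 120-parent target equals 3.33 per programme, 24 parents short of the 144 that Green requires, and the value has no literal category. No other part of the document reconciles the figures. The conclusion rests on the three-course aim being met and on three control equivalents per control centre; the HENRY arm alone gives the same 3.33 if parents split evenly.

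The lack of a minimum total is a conditional weakness: it matters if the denominator is programmes delivered, and the wording leaves that open.

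Severity is moderate. A go/no-go figure is inconsistent with the plan's own target, but no outcome estimate is affected and missing Green is not an automatic stop.

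**What to change.** Reword the parent criterion so that four things are settled.

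1. **Agreement of target and cut-off.** Either keep 4 per programme, restate the expected total as 144 at full delivery (8 x 3 x 4 = 96 with eight centres) and say how 120 is classed; or set Green at a level that 120 parents from 12 centres meets, which at 36 programmes is no higher than 3.33. The second option departs from the yield of four that the article says past experience supports, and leaves a narrow Amber band of 108 to 119 parents at full delivery.
2. **Bands without gaps.** Write Amber as at least 3 and below the Green cut-off.
3. **Denominator.** State whether it is programmes planned or delivered. If delivered, add a total-parents condition. Planned slots are not the only acceptable choice, since they would count an undelivered course as a failure of parent recruitment.
4. **By arm.** Report the criterion for each arm as well as overall, because the third primary objective singles out control centres as having the less defined recruitment pathway.

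The cost is one reworded criterion, with confirmation from the steering committee and the funder, who agreed the present version. No new data are needed.
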